## 4.0 STUDY PROCEDURES AND SCHEDULE

### 4.1 Community presentation and engagement

To facilitate broad understanding and acceptance of the study before implementation, study staff will meet with key individuals in all study villages, heads of all households, religious leaders, community health workers and elderly women, to provide detailed information on the study objectives and procedures prior to the start of enrollment. Presentation of the study in this manner is intended to support high levels of participation and retention in study activities.

### 4.2 Recruitment schedule

Recruitment will take place in 10 outpatient therapeutic feeding centers over a minimum of 12 months.

### 4.3 Evaluation of eligibility

Evaluation of eligibility will occur at the time of first visit/admission to the study outpatient therapeutic feeding centers. Upon arrival, program staff will screen children for eligibility for outpatient treatment as per standard protocol (e.g. age 6 to 59 months; MUAC < 115 mm or grade 1-2 edema; and absence of illness requiring inpatient management). Anthropometry (weight to the nearest 100 g; length (children <24 months) or stature (children ≥ 24 months) to the nearest 0.1 cm; and MUAC to the nearest 0.1 cm using the UNICEF band) will be assessed by program staff using standard techniques described for the WHO Multicenter Growth Reference Study. All study and program staff will be trained and standardized prior to beginning data collection. Standardization sessions will be repeated every 3 months during data collection. Children ineligible for outpatient treatment will not be admitted for nutritional therapy and asked to return home, with explanation of the program admission criteria. These children may be referred to the primary pediatric care program or vaccination program, as needed.

If the child is eligible for outpatient treatment, a study nurse will evaluate the specific study inclusion and exclusion criterion (e.g. new admission, no peanut allergy). If a child presenting to a site assigned to weekly follow-up is eligible for SAM treatment but found ineligible for study inclusion, the child will receive all medical and nutritional treatment with standard weekly follow up at the same site without participating in study data collections. If a child presenting to a site assigned to monthly follow-up is eligible for SAM treatment but does not participate in the study (e.g. parent declines to provide consent or child does not meet inclusion criteria), the child will receive all medical and nutritional treatment with standard weekly follow up at the same site without participating in study data collections. Non-participating children seeking care at sites assigned to monthly follow-up will receive standard care, while all other eligible and participating children included at the monthly site will continue to receive the alternative monthly follow-up as per the random assignment of the site.

#### 4.4 Informed consent

Following eligibility screening, a study nurse will introduce the study and ask if the parent/legal guardian would like to hear more about the study procedures. If the parent/legal guardian wishes to know more about the study, the research nurse will proceed with the consent process. A brief recruitment script is included in the Notice of Information.

The Notice of Information and Informed Consent Form will be read and discussed with all parents / legal guardians in their native language. If the parent / legal guardian is illiterate, a literate witness not connected to the research team will be present and sign and date the consent form to attest the consent process appears to be fair and the parent / guardian voluntarily agrees to participate. The parent / legal guardian will confirm voluntarily participation by signature or witnessed thumbprint.

A unique study identification number will be assigned to each participating child only after completion of the written informed consent procedures. An identification bracelet will be placed on the child and an identification card provided to the caregiver to facilitate identification of the child within the study at subsequent follow up and in the event of transfer to hospital. The identification card and bracelet will include the child's study identification number but no other identifying information.

Note: informed consent preceding enrollment in the outpatient intervention study will be sought at all 10 outpatient therapeutic feeding centers. If a child is directly admitted to inpatient care (e.g. is not already consented and enrolled in the outpatient intervention study), separate informed consent will also be sought from at least one legal guardian or parent of children in order to specifically collect costing data related to inpatient treatment. When the hospitalized child is transferred from inpatient to outpatient care after stabilization, separate and full informed consent for enrollment in the outpatient intervention study will be sought at the time of outpatient admission.

#### 4.5 Completion of admission visit

All caregivers providing consent will be interviewed with regard to socioeconomic/household characteristics and their knowledge, attitudes and practices related to surveillance of clinical danger signs.

At sites assigned to monthly follow up, a study nurse will also provide a short educational session to caregivers describing key danger signs for which the caregiver should return to the site for clinical evaluation, instruct caregivers how to monitor changes in MUAC at home, and introduce the take-home visual aids. Educational sessions may be provided individually or in small groups as needed, with the aim of reducing the wait time of caregivers while not diminishing the quality of training provided. The assessment of caregiver knowledge, attitudes and practices related to surveillance of clinical danger signs will be repeated after the educational session. Caregiver responses to the assessment conducted after the educational session will be reviewed with caregivers to insure correct comprehension of each danger sign

for home surveillance. Caregivers will be reminded to return to the outpatient therapeutic feeding center if they believe their child's condition worsens between scheduled study visits.

Note: children transferred from inpatient to outpatient care after stabilization will be eligible for enrollment at the time of outpatient admission. These children will follow the same enrollment activities described above, but follow-up will differ in that children treated at sites assigned to the monthly follow-up group will be asked to return at 1, 4, 8, 10 and 12 weeks until discharge.

At the end of the admission visit at all sites, the caregiver and child will receive all routine medicines and nutritional treatment sufficient until the next scheduled follow-up. RUTF provided to children enrolled in the study will be marked with a unique marking to facilitate identification of RUTF specifically provided by the study. At the end of the admission visit, compensation (e.g. 2 pieces of soap) for participation in the study will be provided to caregivers.

#### 4.6 Follow-up visits

At sites assigned to standard weekly follow up, follow up visits at the study sites will be scheduled every week until discharge from the nutrition program for a maximum of 12 weeks. At sites assigned to the monthly follow up, follow up visits at the study sites will be scheduled at 4, 8, 10 and 12 weeks until discharge from the nutritional program. At all follow up visits, program staff will measure appetite, weight, height/length (discharge only), MUAC, edema and conduct a clinical examination.

The child will be referred to the inpatient center during follow-up for weight/edema changes (weight loss over 3 weeks; static weight over 4 weeks; onset of edema when previously absent; persistent edema 3 weeks following admission); failed appetite test; or clinical complication necessitating inpatient care (fever, hypothermia, severe dehydration, repeated vomiting, severe respiratory distress, chest in-drawing, severe pallor with respiratory distress, malaria with signs of severity, abscess or extended skin lesions, very weak, apathy or unconscious, or convulsions). A child admitted for inpatient care will be followed on a daily basis at the hospital while receiving inpatient treatment. After stabilization, the child will resume outpatient management and study follow-up at his/her assigned outpatient facility. If the child's outpatient site was assigned to the monthly follow-up group, the child referred from inpatient care will be asked to return to the study site for outpatient management at 1, 4, 8, 10 and 12 weeks until discharge.

All caregivers will be instructed to return to the health center between scheduled visits if any clinical sign of concern develops at home. Spontaneous visits to a study health facility will be recorded with determination of the reason and treatment(s) provided.

At all follow-up visits, to understand utilization of the nutritional supplements in the household, all care givers will be asked to report average daily use of the supplement and return all finished and unfinished product.

At the discharge visit, caregivers knowledge, attitudes and practices related to the key danger signs and MUAC assessment for home-based surveillance will be assessed by standardized questionnaire (see Annex 9.2) in both the weekly and monthly follow-up groups. Compensation (e.g. 2 pieces of soap) for participation in the study will be provided to caregivers at the end of the discharge visit.

#### 4.7 Unannounced safety visits within 2 weeks following inclusion

All children in both groups will receive an unannounced home visit by a study community health worker within the first two weeks of treatment. At each unannounced visit, the community health worker will directly observe RUTF stocks remaining at home, recording the number of sachets available in a household, and will assess the child's MUAC, edema, and his/her clinical condition using a structured questionnaire (see Annex 9.2).

#### 4.8 Tracing for missed visits (absences) and defaulting

We anticipate a non-negligible proportion of children will miss a scheduled visit and require tracing at home. The tracing of these children will be essential to insure complete data for a comparison of intervention groups.

To facilitate tracing of children for home visits, standard care includes notation of the child's residence (ward and area) and caregiver's name in the program registration book at admission. On a weekly basis at routine weekly meetings, program staff will inform community health worker volunteers of children who have missed scheduled visits in the previous week, and all children with a missed visit will be visited at home the following week. If the child is not present at the time of the home visit, relatives or neighbors will be contacted to collect information on vital status of the child if known.

As per standard care, and regardless of intervention assignment, all study children who have missed a scheduled visit will receive a home visit by a community health worker, who will determine vital status of the child and the reason for the missed visit. The community health worker will request the caregiver to return to the study site with the child as soon as possible for the scheduled medical and nutritional follow-up.

A child is considered as a "defaulter" after 3 consecutive missed visits in the weekly follow-up group, and after 1 missed visit in the monthly follow-up group. (e.g. maximum 3 weeks in the weekly follow-up group and maximum 4 weeks in the monthly follow-up group). No difference in the incidence/risk of complications is expected between the weekly and monthly follow-up groups due to the randomization. No difference in the detection of complications between groups is expected under the assumption that caregivers, with the educational session and take

home materials provided, will be able to detect key danger signs at home in a manner similar to that observed at a health facility.

All defaulters will be visited at home by a study community health worker, who will determine vital status of the child and the reason for defaulting.

In the event of death, the Field Investigator will interview the family to obtain the cause of death using verbal autopsy methods and efforts will be made to retrieve medical records if the deceased was admitted to hospital.

#### 4.9 Post-discharge follow-up

All children will receive a home visit by a community health worker 3 months following discharge from the nutritional program, regardless of type of discharge (e.g. recovered, default or non-recovered), requesting the caregiver and child to return to the outpatient therapeutic center. At each post-discharge visit, anthropometric measures (e.g. weight, height and MUAC) will be taken; history of nutritional treatment within the last 3 months will be assessed by maternal report; and caregivers knowledge, attitudes and practices related to the key danger signs and MUAC assessment will be assessed by standardized questionnaire (see Annex 9.2). Compensation (e.g. 2 pieces of soap) for participation in the post-discharge visit will be provided to caregivers at the end of the visit.

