### 3.0 METHODOLOGY

#### 3.1 Study design

This study will be conducted as a stratified cluster randomized trial of a monthly schedule of follow up in the treatment of uncomplicated SAM among children aged 6 to 59 months. The unit of randomization will be the outpatient therapeutic feeding center. The 10 health centers supported by UNICEF will be stratified by size ( $\pm 500$  admissions per site), and centers within a stratum will be randomized in a 1:1 ratio to one of two schedules of treatment: (1) standard weekly visits or (2) monthly visits with support for home-based surveillance.

Distribution of the therapeutic feeding rations, as well as medical and anthropometric surveillance, will take place on a weekly or monthly basis until discharge according to the random assignment of the site. Caregivers in the monthly visit group will receive additional instruction at admission regarding home-based MUAC measurement and clinical surveillance.

Regardless of intervention assignment, all children with uncomplicated SAM will receive standard medical care on admission as per national guidelines, and a home visit 3 months following discharge from the nutritional program. Additional data collection, including coverage assessment and economic costing analysis will be used to address the secondary objectives related to the evaluation of coverage and cost-effectiveness, respectively.

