#### 4.11 Timeline

The total duration of proposed study is 36 months. The study timeline is summarized below.

|                                                   |                        |
|---------------------------------------------------|------------------------|
| 1. Development and validation of education tools: | 2014 (Niger)           |
| 2. Protocol and questionnaire development:        | February – March 2017  |
| 3. Ethical review:                                | March 2017             |
| 4. Staff recruitment and training:                | April – May 2017       |
| 5. Adaptation of study tools to local context:    | April – May 2017       |
| 6. Pilot phase begins:                            | June 2017              |
| 7. Study enrollment begins:                       | March 2018             |
| 8. Enrollment complete:                           | February 2019          |
| 9. Facility-based follow-up complete:             | April 2019             |
| 10. Home-based follow-up post discharge complete: | July 2019              |
| 11. Data analysis and reporting:                  | August – December 2019 |
| 12. Dissemination:                                | January 2020           |

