## 7.0 ADMINISTRATIVE AND LOGISTICAL CONSIDERATIONS

### 7.1 Human resources

Each site will have a study team comprised of 2 study nurses, who will help take informed consent, collect background information at admission, and support high quality data collection at all enrollment and follow up visits, and 1 nutritional assistant who will support anthropometric assessment and data collection at all enrollment and follow up visits. There will be an additional study nurse assigned to the inpatient center, as well as 2 nurse supervisors to oversee activities at 5 sites each. Community health workers will conduct tracing of patients who do not attend regularly scheduled follow up and complete the unannounced safety visits, and issue reminders for the post-discharge follow-up visits. Four data entry clerks, under the supervision of a data manager, will conduct continuous double-data entry, comparison and cleaning. Members of the study team will be recruited locally for the duration of the study (approximately 19 months).

All locally recruited staff will be under the direct supervision of the Field Investigator, a trained medical doctor with experience in epidemiological research. The Field Investigator, recruited by Epicentre, will be responsible for the training and supervision of study staff and for coordination of all logistics and data collection activities in accordance with the study protocol and standard operating procedures.

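### Under section 4.9 the relapse endpoint is collected only from families who return to the center at 3 months, with no stated fallback or vital-status record, while section 3.1 and the timeline describe home follow-up.

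*Protocol*

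**What the plan says.** Section 4.9 makes the 3-month contact universal: "All children will receive a home visit by a community health worker 3 months following discharge from the nutritional program, regardless of type of discharge". The worker's stated purpose at the home is "requesting the caregiver and child to return to the outpatient therapeutic center". The section then lists what happens at the post-discharge visit: "At each post-discharge visit, anthropometric measures (e.g. weight, height and MUAC) will be taken", followed by the maternal report of nutritional treatment since discharge, the knowledge questionnaire, and soap at the end.

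Section 7.1 gives community health workers the same limited role: they "issue reminders for the post-discharge follow-up visits".

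Two other places read differently. Section 3.1 says that all children receive "a home visit 3 months following discharge from the nutritional program" and mentions no return to the center. The timeline in section 4.11 has the milestone "10. Home-based follow-up post discharge complete", listed directly after a separate milestone for facility-based follow-up.

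Section 2.0 defines relapse solely by the mother's report of admission to a therapeutic feeding program within 3 months of discharge. It is a named secondary endpoint with its own secondary objective.

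**The concern.** The worker is due at every child's home at the time the relapse endpoint falls due. The endpoint needs one question to the caregiver, yet section 4.9 places that question at a later visit that requires travel. Nothing is said about a family that does not come, and section 4.9 does not ask the worker to record whether the child is alive.

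Three consequences follow.

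- Relapse would be observed in a self-selected subset. Section 4.9 deliberately includes defaulters, who have already stopped attending, and the rationale in sections 1.1 to 1.3 is that facility travel is hard for many of the families the schedule is meant for.
- Without vital status, a child who did not return because of death cannot be told apart from one who did not return for another reason, so the denominator for relapse is unclear.
- Because the text describes the contact in two ways, sites could collect the endpoint differently, some at home and some at the center.

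Section 3.9 promises intention-to-treat analysis for all outcomes. That is hard to honor for an endpoint recorded only in those who return.

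**Working it through.** **Where the assessment takes place**

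| Place in protocol | What it implies |
|---|---|
| 4.9 | Home contact to request a return; measures and relapse history at the post-discharge visit |
| 7.1 | Worker reminds families of the visit |
| 5.5 | Soap is justified by facility attendance; the post-discharge visit is among those rewarded |
| 3.1 | Home visit, no return mentioned |
| 4.11 | Home-based follow-up, listed apart from facility-based follow-up |
| Abstract | A visit to assess anthropometry; no place named, so neutral |

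Sections 4.9 and 7.1 are the most specific and they agree, so the center-based reading is the natural one. Section 3.1 can be squared with it, since a home visit is made, but it leaves out the return. The timeline entry is the clearest conflict.

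**What workers do at home elsewhere**

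At the unannounced visit in the first two weeks (section 4.7) the worker "will assess the child's MUAC, edema, and his/her clinical condition using a structured questionnaire". After missed visits (section 4.8) workers determine vital status, and ask relatives or neighbors if the child is absent. Section 4.9 asks for neither. Even if the tracing in section 4.8 were extended to 3 months, it would yield vital status and the reason for absence, not relapse.

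**How far selective return could move the relapse estimate**

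The protocol has no figure to reproduce here, because it states neither a relapse risk nor 3-month attendance. The inputs below are therefore assumptions. Let r be the true relapse risk, a1 the attendance of relapsed children and a0 the attendance of the others. Among those who return:

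observed risk = r × a1 / (r × a1 + (1 − r) × a0)

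With r = 0.10, a0 = 0.80 and a1 = 0.60: 0.060 / (0.060 + 0.720) = 7.7%. The range with a0 = 0.80 is:

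| a1 | True 10% observed as | True 5% observed as |
|---|---|---|
| 0.80 | 10.0% | 5.0% |
| 0.60 | 7.7% | 3.8% |
| 0.40 | 5.3% | 2.6% |
| 0.95 | 11.7% | 5.9% |

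The estimate can be too low or too high. The comparison between arms is distorted when the attendance pattern differs by arm. Suppose both arms have a true risk of 10% and a0 = 0.80. If a1 = 0.80 in one arm and 0.60 in the other, the arms show 10.0% and 7.7%, a spurious difference of 10.0 − 7.7 = 2.3 percentage points. If instead the second arm has a1 = 0.95, the spurious difference is 11.7 − 10.0 = 1.7 points the other way.

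**The case against.** Center-based anthropometry by trained, standardized staff is a defensible choice, and nothing here argues against it. Several stronger readings are tempting, but the documents do not support them.

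- **That the children who died, relapsed or are hard to reach are the ones lost.** This is inference. Every household is visited, so a death would probably become known, and the verbal autopsy sentence in section 4.8 is not worded as limited to the treatment period. By definition a relapsed child has been readmitted to a program and may be easier to find. Selective loss is most plausible for families with difficult travel, but its direction is not established.
- **That attendance differs by arm.** No passage says so. It is possible, for instance because defaulting is defined differently in the two arms and the mix of discharge types may therefore differ, but that is a conjecture.
- **That a fifth of children would lack 3-month data.** The 20% in section 3.7 is the loss allowance in the power calculation for recovery. It is not a forecast for this visit.
- **That edema is not assessed at 3 months.** The wording is "anthropometric measures (e.g. weight, height and MUAC) will be taken", a list of examples, and the case report forms are not shown. Edema is unnamed, which is a smaller point. It enters no listed endpoint at 3 months.
- **That the worker records nothing at the home.** Section 4.9 is silent on this, and silence is not a prohibition.

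What stands after these concessions is the conflict between sections, the lack of any fallback for families who do not return, and the absence in section 4.9 of an instruction to record vital status or readmission at the home.

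**Conclusion.** The point holds for a secondary endpoint. Sections 4.9 and 7.1 put the relapse question at a return visit to the center, section 3.1 and the timeline describe home follow-up, and the passages need to be reconciled. Under section 4.9 as written, relapse is observed only in families who return, so the comparison is exposed to non-random missing data.

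The size and direction of any bias cannot be derived from the documents. The tabulated 5.3% to 11.7% for a true 10% rests entirely on the assumed attendance rates and shows sensitivity only. The primary endpoint, recovery, is not affected. The change is worth making because the exposure is avoidable at a visit that is already planned.

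**What to change.** 1. Reconcile sections 3.1, 4.9, 4.11 and 7.1, so that each says what is done at the home and what is done at the center.
2. In section 4.9, have the community health worker complete a short form at the 3-month home visit, for every child in both arms. It should record vital status, with date of death where applicable, and the caregiver's report of any admission to a therapeutic feeding program since discharge.
3. Use this home report as the source of the relapse endpoint in both arms, so that ascertainment does not depend on travel.
4. Keep anthropometry and the knowledge questionnaire at the center. Home MUAC and edema for families who do not return is optional, since it changes no listed endpoint.

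The cost is one short form, a few more minutes per home visit and the matching data entry. No extra visit or staff should be needed, since the visit and the workers are already in the plan. Families absent from home would still be missed.
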